**Figure 2. f2:**
[figure not shown]
Cohort flow chart for the DIVIDS (Delhi Infant Vitamin D Supplementation) study, India.

**Figure 3. f3:**
[figure not shown]
Cohort flow chart for SAM (Severe Acute Malnutrition), Lusaka, Zambia.

**Figure 4. f4:**
[figure not shown]
Cohort flow chart for CICADA (Chronic Infections, Co-morbidities and Diabetes in Africa), Mwanza, Tanzania.

**Figure 5. f5:**
[figure not shown]
Cohort flow chart for NUSTART (Nutritional Support for Africans Starting Antiretroviral Therapy), Lusaka, Zambia.

**Figure 6. f6:**
[figure not shown]
Cohort flow chart for St-ATT (Starting Anti-TB Treatment) Cohort, Philippines.

**Figure 7. f7:**
[figure not shown]
Cohort flow chart for CLHNS (Cebu Longitudinal Health and Nutrition Survey), Philippines.

### Participant recruitment

Cohort members or their guardians (in case of children) will be contacted by the site principal investigators using the participant contact details from their most recent follow-ups. They will be asked if they wish to participate in SAMPA, and written informed consent will be obtained. For NUSTART, Lusaka, we will need to recruit never-malnourished controls. There are several possible levels of participation in SAMPA, based on cohort, sample size needed for testing specific hypotheses, and individual participants’ willingness to consent to specific tests. The potential different levels of participation are below. People not consenting to either version of the OGTT, a) or b), will be considered as not consenting to SAMPA overall and thus ineligible:
a)Questionnaires for socio-economic demographic and dietary assessment; anthropometry and body composition; medical exam; urine and stool sample collection; abdominal ultrasound and OGTT with blood sampling at baseline (fasting), and 15, 30, 45, 60, 90 and 120 minutes after glucose ingestion;b)Questionnaires for socio-economic demographic and dietary assessment; anthropometry and body composition; medical exam; urine and stool sample collection; abdominal ultrasound and minimal OGTT only, that is, with blood sampling at baseline (fasting), and 60 and 120 minutes after glucose ingestion;c)Addition of CT scans to a) or b). Children will not be asked to have CT scans. Women of childbearing age will not be asked to have CT scans unless they consent to a pregnancy test and have a negative result;d)Addition of IVGTT. This will be requested only for subsets of participants in the CICADA cohorts, as detailed below; glucose infusion will be at 0 minutes and samples will be collected at -10, -1, 2, 4, 6, 8, 10 minutes using an indwelling cannula.

Regarding point c) above, although children in the DIVIDS cohort will not have CT scans, 100 of them will have MRI scans, funded by a separate project, which will be able to assess pancreas size and structure, as well as visceral fat.

### Outcome measures

*Primary outcome measures*
1.Pancreatic endocrine function: diabetes or impaired glucose tolerance (pre-diabetes) by OGTT or HbA1c, defined using World Health Organization (WHO) cut-offs
^
23
^
2.Pancreatic exocrine function: faecal elastase and serum lipase

*Secondary outcome measures*
1.Pancreas size and structure: Pancreas size and architecture using ultrasound and CT (subsets from all adult cohorts)2.Pancreatic calcification: Calcification determined by CT scan (subsets from all adult cohorts)3.Insulin production and insulin resistance:a.Mathematical modelling of blood glucose, insulin and C-peptide at three (for children) or seven (for adults) times during a 120-minute OGTT for estimation of indices of first phase, second phase and total insulin release, insulin kinetics and insulin resistance;b.Mathematical modelling of data from analytes from IVGTT measured in blood samples collected at -10, -1, 2, 4, 6, 8, 10 minutes: glucose, insulin, and C-peptide (subset from CICADA
*).*
4.Other hormonal contribution to glucose metabolism and diabetes: Incretins (gastric inhibitory polypeptide (GIP) and glucagon-like peptide-1 (GLP-1)) and glucagon at 0, 30, 60, 90 and 120 minutes during an OGTT (subsets from CICADA and St-ATT). The goal is to assess whether insulin resistance is associated with changes in endocrine signals from the gut. The area under the curve of glucagon (AUC glucagon) will be used to assess a possible presence of hyperglucagonemia, often seen in T2D subjects.5.Proinsulin: Proinsulin in baseline samples before OGTT. The baseline proinsulin levels will be used as indicator of β-cell stress/exhaustion in the fasting state where higher levels of proinsulin will indicate higher levels of β-cell stress.6.Abnormal prior pro-insulin/insulin ratio and diabetes (subset): From the CICADA cohort, measurement of pro-insulin and insulin in fasting samples collected four years previously and comparison with current diabetes by OGTT. Like the fasting proinsulin, the pro-insulin/insulin ratio in fasting samples will be used as a surrogate measure of β-cell stress.

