## Introduction

There is an increasing prevalence of overweight and obesity worldwide which is associated with increases in non-communicable diseases (NCDs), including diabetes.
^
1
^ Meanwhile, wasting malnutrition remains common in low- and middle-income countries (LMICs).
^
2
^ It is well-documented that prenatal malnutrition, usually measured as low birth weight, can increase the risk of NCDs in later life,
^
3
^ but how wasting malnutrition in childhood or adulthood may affect long-term health is less studied.
^
4
^ The issue of child or adult malnutrition's long-term implications is becoming increasingly important because more children survive severe acute malnutrition as a result of improved care, while pharmacological treatments for infections, such as HIV and tuberculosis, that commonly cause or are linked with malnutrition, have increased patient survival among all age groups. Evidence from a recent systematic review suggests pancreatic endocrine and exocrine functions may not recover fully after childhood or adult wasting malnutrition.
^
5
^ Such long-term effects on the pancreas may contribute to the different phenotype of diabetes common in LMICs with prevalent malnutrition, compared with the diabetes phenotype in high-income countries. Diabetes in LMICs often has a relatively early disease onset (<50 years) and may occur at a low or normal body mass index (BMI).
^
6
^ There are heterogeneous reports of atypical diabetes in LMICs, describing an entity of malnutrition-related, insulin-deficient diabetes related to pancreatic damage, for example, a phenotype termed fibrocalculous pancreatic diabetes,
^
7
^ but these studies often report highly selected patients, which can provide mechanistic but not epidemiologic information,
^
8
^ or precede the availability of modern assessment methods.
^
9
^ Our own work has shown that prior malnutrition in Tanzanian adults is associated with lower insulin production in men
^
10
^ and that insulin deficiency is a more common cause of diabetes than insulin resistance.
^
11
^ If malnutrition is associated with an atypical form of diabetes, driven by insulin deficiency and not resistance, then this has major implications for health policy, planning, investigation and treatment of diabetes in LMICs, because current first-line treatments of diabetes in these settings usually use treatments such as metformin which would be inappropriate for insulin-deficient diabetes.

Both pancreatic endocrine (

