### Assessments

The following assessments will be carried out on all consenting participants across the cohorts. Target sample sizes are as in
Table 1.
1.
**
*OGTT:*
** The primary outcome for comparing those with and without prior malnutrition across all cohorts will be glucose ≥ 7.8 mmol/L at 2 hours in a standard OGTT with 75 g glucose (in children, 1.75 g/kg body weight up to 75 g) that is, diabetes plus impaired glucose tolerance by WHO criteria.
^
23
^ Glucose in one hour samples in all participants will also be measured since this may be a better predictor of progression to diabetes due to insulin deficiency than the two-hour time point.
^
24
^ Those with OGTT compatible with diabetes will be called back for a repeat OGTT in order to determine need for referral for clinical care. Urine dipstick will also be done for ketones to assess potential need for (short-/long-term) insulin replacement therapy. Indices of beta-cell function, insulin kinetics, and insulin resistance will be modelled from glucose, insulin and C-peptide during OGTT.
^
25
^
^,^
^
26
^ Proinsulin will be measured in baseline samples only. Autoantibodies will be measured in participants with OGTT indicative of diabetes to confirm/exclude autoimmune type-1 diabetes.2.
**
*HbA1c*
**: This will be by point-of-care test (Hemocue, Angelholm, Sweden) using fingerprick blood samples for most cohorts to indicate long-term glycaemic control; for the DIVIDS cohort, HbA1c will be measured in venous blood by a commercial lab ([name] Labs, Delhi).3.
**
*Abdominal ultrasound*:** Ultrasound scans will be performed by trained sonographers or radiologists in identified health facilities. The participant will be asked to lie on the ultrasound examination bed. They will be asked to breathe in and hold their breath in order to optimise visualization of the pancreas. A curvilinear ultrasound probe (2-5 MHz) will be placed onto the participant’s abdominal wall in the upper abdomen to image the pancreas. Images of the pancreas will be recorded and saved. Parameters obtained from the scans will be pancreas size, duct size, calcification, or other abnormality.4.
**
*Exocrine pancreas markers:*
** These will be serum lipase in baseline OGTT samples and faecal elastase: Participants will collect faecal samples either in the clinic or bring them from home.5.
**
*Urine glucose and ketones by dipstick*
**: These will be from random urine collection.6.
**

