^3^)•Abnormalities in duct size•Presence of cysts or calcification.Standardisation of the measurements between sites will be assured by consultation among all site radiologists of 10 scans from each cohort. The studies will be conducted and reviewed for incidental findings at the local site in accordance with the relevant standard operating procedure (SOP).11.
**
*Proinsulin-insulin ratio*
**: This will be done in 120 archived samples from the CICADA cohort which were collected from fasting participants about four years prior to the SAMPA visit.

The DIVIDS child cohort will not have CT scans but 100 children will have MRI scans, funded through a separate project, which will permit examination of pancreas size and structure as well as quantification of visceral fat. Also, in the DIVIDS cohort only, we will measure full blood count, blood lipids and C-reactive protein in baseline samples from the OGTT; this is done for purposes of local ethics and family desire for the information.

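### Secondary outcome 5 reads the raw fasting proinsulin level as beta-cell stress in one direction, although the study expects insulin output to differ between the groups compared

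*Protocol article*

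**What the plan says.** All references are to the protocol article.

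- **Outcome measures, secondary outcome 5.** "The baseline proinsulin levels will be used as indicator of β-cell stress/exhaustion in the fasting state", and the reading is fixed: "higher levels of proinsulin will indicate higher levels of" beta-cell stress. No scaling to insulin or C-peptide is named.
- **Outcome measures, secondary outcome 6.** For the archived CICADA samples, "the pro-insulin/insulin ratio in fasting samples will be used as a surrogate measure of β-cell stress". The text presents this as a marker of the same kind as fasting proinsulin.
- **Assessments.** The ratio is confined to stored material: "This will be done in 120 archived samples from the CICADA cohort". At the SAMPA visit, "Proinsulin will be measured in baseline samples only".
- **Outcome measures, secondary outcome 3.** Insulin and C-peptide are measured in the same test: "Mathematical modelling of blood glucose, insulin and C-peptide at three (for children) or seven (for adults) times during a 120-minute OGTT". Participant recruitment shows that both OGTT schedules include the fasting sample.
- **Introduction.** The team's own earlier work found that "prior malnutrition in Tanzanian adults is associated with lower insulin production in men". Hypothesis 3 likewise expects a relative lack of insulin after wasting, with or without insulin resistance.

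**The concern.** A raw proinsulin level carries two things at once: how much insulin is circulating, and how much unprocessed precursor accompanies each unit of it. It can serve as a one-directional stress marker between groups if their insulin levels are similar. This study is built on the expectation that they may not be.

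If previously malnourished participants have lower fasting insulin, a true rise in their proinsulin/insulin ratio can be masked or reversed in the raw level. If insulin resistance raises insulin in some participants, the raw level can rise with no change in the ratio and be taken for stress. At stake is the direction of the conclusion drawn from one secondary outcome.

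**Working it through.** Outcome 5 has no sample size or power figure of its own, so there is none to reproduce. The check asks when the raw level and the ratio disagree.

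**Inputs**
- Ratio difference 0.04 and SD 0.07: from the Hypothesis 4 sample size. There, 0.04 is the difference between people with later diabetes and controls. It is borrowed here only as a scale that the study itself treats as relevant.
- Control ratio *r*: not in the documents; assumed 0.10 to 0.30.
- Proportional deficit in fasting insulin *f*: not in the documents; varied.

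**Formula.** By definition, proinsulin = insulin × ratio. If insulin and ratio are independent within each group, mean proinsulin in the exposed group relative to control is

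(1 − *f*) × (*r* + 0.04) / *r*.

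This falls below 1 when *f* > 0.04 / (*r* + 0.04).

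| Control ratio *r* (assumed) | Deficit above which proinsulin is lower despite the higher ratio |
|---|---|
| 0.10 | 0.04/0.14 = 29% |
| 0.15 | 0.04/0.19 = 21% |
| 0.20 | 0.04/0.24 = 17% |
| 0.30 | 0.04/0.34 = 12% |

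**Masking before reversal, at *r* = 0.15**
- *f* = 0: 0.19/0.15 = 1.27
- *f* = 10%: 0.9 × 0.19/0.15 = 1.14
- *f* = 20%: 0.8 × 0.19/0.15 = 1.01
- *f* = 30%: 0.7 × 0.19/0.15 = 0.89

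A 20% deficit removes almost all of the signal, and a 30% deficit reverses it.

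**The other direction.** At *r* = 0.15, insulin 27% higher with an unchanged ratio gives proinsulin 1.27 times control. That is the same value as a 0.04 rise in the ratio at equal insulin, so the raw level cannot tell the two apart.

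**How often a test would mislead.** A simulation used 1,000 runs per setting, 200 per group, ratio SD 0.07 and an assumed SD of 0.6 for log insulin, and tested log proinsulin.

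| *r* | Deficit | Proinsulin significantly lower | Proinsulin significantly higher |
|---|---|---|---|
| 0.10 | 30% | 0.2% | 12.3% |
| 0.10 | 40% | 16.7% | 0% |
| 0.15 | 0% | 0% | 96% |
| 0.15 | 20% | 0.6% | 9.4% |
| 0.15 | 30% | 23.5% | 0.2% |
| 0.20 | 30% | 64% | 0% |

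The ratio test was significantly higher in at least 99.9% of runs in these settings. That is by construction, because the effect was placed in the ratio. It shows that the raw level can miss or reverse such an effect, not that the ratio is the true measure of stress. The test is on the log scale, so its crossing point lies somewhat above the threshold for means, which explains the row for *r* = 0.10 at 30%.

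**The case against.** The strongest reply is that outcome 5 is a supporting secondary marker, that both candidate markers are imperfect surrogates, and that an article may leave derived indices to a fuller plan. Much of this stands.

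- **The ratio is not the truth.** Its denominator depends on insulin clearance, which this study models as potentially altered. This argues for adding the ratio with a C-peptide check, and against simply replacing the raw level.
- **The sizes are assumed.** The documents give no control ratio and no insulin deficit, the Introduction's finding concerns men only, and it speaks of insulin production, not fasting concentration. With no deficit, raw proinsulin was significantly higher in 54% to over 99% of simulated runs.
- **No low-level rule is written.** The text says that higher means more stress. That lower means less is the natural converse, but no cut-off or score is set.
- **An SAP may add indices.** It may. The point here is a rule of interpretation that the article states, not an omission.

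A reader might also infer three stronger claims, which the documents do not support:

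- *That exposed participants are leaner.* The discussion of BMI and fat mass under Hypothesis 1 allows for excess fat after recovery.
- *That Objective 3 is compromised.* Its indices come from modelled glucose, insulin and C-peptide, with HOMA-IR and liver fat. Proinsulin is not among them.
- *That outcomes 5 and 6 must be comparable.* Outcome 6 is a separate nested case-control question on samples about four years old, and no comparison with outcome 5 is planned.

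**Conclusion.** The point holds in a limited form. The protocol fixes a one-directional reading of an unscaled precursor level while expecting lower insulin output in the exposed group. Under that expectation the raw level can hide or reverse a rise in the proinsulin/insulin ratio, and where output is raised it can suggest stress without one. For a ratio rise of 0.04, reversal of the mean needs an insulin deficit above about 12% to 29%, for assumed control ratios of 0.30 down to 0.10.

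This rests on the identity between the three quantities, on independence of insulin and ratio within groups, and on assumed values of both unknowns. It does not rest on the ratio being a perfect measure. It is enough that the protocol accepts the ratio as a surrogate for the same construct. The consequence is confined to the interpretation of one secondary outcome, and no stated hypothesis test depends on it.

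**What to change.** For the SAMPA baseline samples, amend secondary outcome 5 to:

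1. add the fasting proinsulin/insulin ratio, the surrogate already used in outcome 6;
2. add fasting proinsulin/C-peptide as a check, because insulin clearance may differ between groups;
3. report raw proinsulin beside both;
4. replace the fixed reading with a statement that raw proinsulin alone will not be interpreted as higher or lower beta-cell stress.

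Proinsulin, insulin and C-peptide are already to be measured at the fasting time point, so no sample or assay is added. The cost is a sentence or two in the outcome definition and a little extra analysis. The indices may disagree. If they do, all three should be reported, with insulin output and clearance considered as explanations.

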### Assessments

The following assessments will be carried out on all consenting participants across the cohorts. Target sample sizes are as in
Table 1.
1.
**
*OGTT:*
** The primary outcome for comparing those with and without prior malnutrition across all cohorts will be glucose ≥ 7.8 mmol/L at 2 hours in a standard OGTT with 75 g glucose (in children, 1.75 g/kg body weight up to 75 g) that is, diabetes plus impaired glucose tolerance by WHO criteria.
^
23
^ Glucose in one hour samples in all participants will also be measured since this may be a better predictor of progression to diabetes due to insulin deficiency than the two-hour time point.
^
24
^ Those with OGTT compatible with diabetes will be called back for a repeat OGTT in order to determine need for referral for clinical care. Urine dipstick will also be done for ketones to assess potential need for (short-/long-term) insulin replacement therapy. Indices of beta-cell function, insulin kinetics, and insulin resistance will be modelled from glucose, insulin and C-peptide during OGTT.
^
25
^
^,^
^
26
^ Proinsulin will be measured in baseline samples only. Autoantibodies will be measured in participants with OGTT indicative of diabetes to confirm/exclude autoimmune type-1 diabetes.2.
**
*HbA1c*
**: This will be by point-of-care test (Hemocue, Angelholm, Sweden) using fingerprick blood samples for most cohorts to indicate long-term glycaemic control; for the DIVIDS cohort, HbA1c will be measured in venous blood by a commercial lab ([name] Labs, Delhi).3.
**
*Abdominal ultrasound*:** Ultrasound scans will be performed by trained sonographers or radiologists in identified health facilities. The participant will be asked to lie on the ultrasound examination bed. They will be asked to breathe in and hold their breath in order to optimise visualization of the pancreas. A curvilinear ultrasound probe (2-5 MHz) will be placed onto the participant’s abdominal wall in the upper abdomen to image the pancreas. Images of the pancreas will be recorded and saved. Parameters obtained from the scans will be pancreas size, duct size, calcification, or other abnormality.4.
**
*Exocrine pancreas markers:*
** These will be serum lipase in baseline OGTT samples and faecal elastase: Participants will collect faecal samples either in the clinic or bring them from home.5.
**
*Urine glucose and ketones by dipstick*
**: These will be from random urine collection.6.
**
*Anthropometry*:** Anthropometry will use standard methods
^
27
^ conducted by trained staff. At each site technical error of measurement will be assessed and further training provided so that all staff reach acceptable levels of agreement with the local criterion anthropometrist.
^
28
^ Anthropometric measurements will be weight, height, sitting height, tibia length, circumferences of waist, hip and mid-upper arm, and triceps and subscapular skinfold thicknesses.7.
**
*Body composition:*
** All sites will use bioelectrical impedance (BIA) for body composition assessment. Lusaka will additionally use air displacement plethysmography (BodPod) and can assess its agreement with BIA.

The following assessments will be conducted in only subsets of consenting participants.
8.
**
*Detailed OGTT*
**: The same OGTT protocol will be used as above but, for 80 participants in each of the CICADA and St-ATT cohorts, referred to as the in-depth subset, we will measure additional hormones: glucagon, gastric inhibitory peptide (GIP), glucagon-like peptide-1 (GLP-1) at multiple time points and trypsinogen in baseline samples. The in-depth subsets will be randomly selected from the cohort participants, stratified by whether or not they were recorded as previously malnourished in our databases from earlier follow-ups. In event of refusals, replacements will be from the next in the randomised lists.9.
**
*IVGTT:*
** This test is the gold standard for estimating the early insulin response. It will be done only in the in-depth subset from CICADA. Results will be compared with OGTT in the same participants in order to better understand the OGTT results. For this test a solution of sterile 50% dextrose, in amounts 0.3 g/kg body weight, will be injected into the antecubital vein over 60 seconds starting at time 0 minutes. Blood samples will be taken at -10, -1, 2, 4, 6, 8, 10 minutes for measurement of glucose, insulin, C-peptide and glucagon.10.
**
*CT scans*
**: The CT studies will be performed in 100 participants from each of the adult cohorts by qualified and experienced radiologists in identified health facilities. Participants will be randomly selected, similarly to the in-depth subsets. Scans will be taken without use of contrast agents. The protocol will assess the following:•Pancreatic volume (in cm
^3^)•Abnormalities in duct size•Presence of cysts or calcification.Standardisation of the measurements between sites will be assured by consultation among all site radiologists of 10 scans from each cohort. The studies will be conducted and reviewed for incidental findings at the local site in accordance with the relevant standard operating procedure (SOP).11.
**
*Proinsulin-insulin ratio*
**: This will be done in 120 archived samples from the CICADA cohort which were collected from fasting participants about four years prior to the SAMPA visit.

The DIVIDS child cohort will not have CT scans but 100 children will have MRI scans, funded through a separate project, which will permit examination of pancreas size and structure as well as quantification of visceral fat. Also, in the DIVIDS cohort only, we will measure full blood count, blood lipids and C-reactive protein in baseline samples from the OGTT; this is done for purposes of local ethics and family desire for the information.

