## Protocol

### Study objectives and hypotheses

*Overall hypothesis*

Wasting malnutrition at any age has medium- and long-term detrimental effects on endocrine and exocrine pancreatic function and structure.
1.
**
*Specific objective 1*:** To investigate whether wasting malnutrition at various ages is associated with abnormalities of pancreas structure and function later in life.a.
**
*Hypothesis 1*:** Prior wasting malnutrition is associated with later abnormal pancreatic structure and endocrine and exocrine function.b.
**
*Pancreatic phenotype of interest:*
** Diabetes assessed by oral glucose tolerance test (OGTT) and haemoglobin A1c (HbA1c), exocrine pancreatic function tests (serum lipase, faecal elastase), pancreatic size and architecture measured using ultrasound for all participants and measured using computed tomography (CT) scans for a subset of participants (non-pregnant adult participants).2.
**
*Specific objective 2:*
** To investigate whether pancreatic abnormalities in participants with prior malnutrition and diabetes are analogous to a previously described entity of fibro-calculous diabetes.a.
**
*Hypothesis 2:*
** Prior wasting malnutrition is associated with pancreatic calcification which in turn is associated with diabetes.b.
**
*Pancreatic phenotype of interest:*
** Pancreatic calcifications determined from CT scans among non-pregnant adult study participants.3.
**
*Specific objective 3:*
** To investigate the relative importance of decreased insulin production or increased insulin resistance in malnutrition-associated diabetes.a.
**
*Hypothesis 3:*
** The abnormal glucose regulation seen after wasting malnutrition is associated with relative insulin deficiency with or without insulin resistance.b.
**
*Pancreatic phenotype of interest:*
** Indices of glucose metabolism and insulin kinetics based on mathematical models of glucose and hormone concentrations during OGTT and intravenous glucose tolerance tests (IVGTT). Homeostasis model assessment of insulin resistance (HOMA-IR) and liver fat (insulin resistance) will also be assessed.4.
**
*Specific objective 4:*
** To investigate whether a prior abnormal pro-insulin/insulin ratio is associated with diabetes in adults infected or not with HIV or previously with tuberculosis.a.
**
*Hypothesis 4:*
** An abnormal pro-insulin/insulin ratio is associated with later development of diabetes in adults who had malnutrition earlier in life in association with HIV or tuberculosis infection.b.
**

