### Statistical analyses and sample size calculations

Analyses related to individual hypotheses are described below. Primary analyses will be conducted for each cohort separately. Pooled analyses using all or some cohorts combined will be conducted based on the individual cohort results, and in order to investigate how age at malnutrition and length of time between malnutrition and outcome assessment influence the associations between malnutrition and pancreas structure and function. Analyses will be guided by the conceptual framework in
Figure 1. Sample sizes for the specific hypotheses indicate that, with the available number of participants in the cohorts, we have sufficient power for the main analyses with all participants. For some expensive or labour- and participant-intensive outcomes, we had to consider cost and feasibility and have calculated power for analyses in subsets.

*Hypothesis 1:*
Prior malnutrition is associated with later abnormal pancreatic structure and endocrine and exocrine function.

Participants with and without prior wasting malnutrition, the SAMPA study primary exposure, will be compared within each cohort for all pancreas structure and function outcomes: diabetes by OGTT or HbA1c, exocrine function as indicated by faecal elastase and serum lipase, and pancreas size and presence of abnormalities detected by ultrasound or CT scan. We will initially fit regression models for each outcome with prior malnutrition as the main exposure, controlling for sex and for age as a continuous variable. We will investigate whether there are interactions between prior malnutrition and sex, which is known to be associated with both prior malnutrition and diabetes. We will then investigate whether the associations between malnutrition and the outcomes differ by the following variables:
•Time since malnutrition•Sitting/standing height ratio as an indicator of early life stunting•HIV status for African cohorts only (SAM Lusaka, NUSTART Lusaka, CICADA)

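### The primary endocrine outcome is given as two different events, only one of which was powered, and the 2-hour glucose rule read literally scores some treated diabetes as unaffected

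*Protocol article*

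**What the plan says.** Four places in the Protocol article describe the endocrine outcome, and a fifth powers it.

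- **Outcome measures, primary list:** "Pancreatic endocrine function: diabetes or impaired glucose tolerance (pre-diabetes) by OGTT or HbA1c, defined using World Health Organization (WHO) cut-offs".
- **Assessments, item 1 (OGTT):** "The primary outcome for comparing those with and without prior malnutrition across all cohorts will be glucose ≥ 7.8 mmol/L at 2 hours", explained there as "diabetes plus impaired glucose tolerance by WHO criteria". Item 2 of the same section gives HbA1c a different role: it is measured "to indicate long-term glycaemic control".
- **Statistical analyses, Hypothesis 1:** the outcomes to be regressed on prior malnutrition include "diabetes by OGTT or HbA1c, exocrine function as indicated by faecal elastase and serum lipase". Impaired glucose tolerance is not mentioned.
- **Study objectives, Objective 1:** the phenotype of interest is diabetes assessed by OGTT *and* HbA1c, again without impaired glucose tolerance.
- **Sample size for Hypothesis 1:** a 7% prevalence of OGTT glucose at or above 7.8 mmol/L is assumed in those without malnutrition. CICADA and St-ATT are each said to have 80% power for a 7.5-point difference.

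None of these places says how a participant with previously diagnosed or treated diabetes enters the primary outcome.

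**The concern.** Outcome measures and Assessments both use the word primary, but they name different events. One is a composite of two tests and the other is a single 2-hour glucose value. The analysis text for the same hypothesis then names a third event, with a higher threshold. The definitions can differ in prevalence and in their association with prior malnutrition. With more than one in print, whichever gives the clearest result could be presented as prespecified.

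A second issue follows from the 2-hour rule. It classifies people by one measured glucose value. Someone already diagnosed and treated, whose 2-hour value is below 7.8 mmol/L, has the condition the outcome is meant to capture but is scored as free of it.

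**Working it through.** **1. The definitions side by side.** Each row is a possible participant. The entries show how each text, as worded, would score that person.

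| Participant | Outcome measures (diabetes or pre-diabetes, OGTT or HbA1c) | Assessments (2-hour glucose ≥7.8) | Hypothesis 1 text (diabetes, OGTT or HbA1c) |
|---|---|---|---|
| 2-hour glucose in the impaired range, HbA1c not raised | event | event | not an event |
| HbA1c in the diabetes range, 2-hour glucose <7.8 | event | not an event | event |
| Treated diabetes, 2-hour glucose <7.8, HbA1c raised | event | not an event | event if HbA1c is in the diabetes range |
| Treated diabetes, 2-hour glucose <7.8, HbA1c not raised | not an event | not an event | not an event |

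Objective 1's *and*, taken strictly, would require both tests to be positive and so differs again. The first two rows are enough to show that the definitions are not restatements of one event. The last row shows that treated diabetes can be missed under all three. The 2-hour rule misses it most widely, because HbA1c cannot bring the person back in.

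**2. Which version was powered.** Inputs:
- rates of 7% and 7% + 7.5% = 14.5% (sample size text);
- St-ATT, 600 expected (Table 1), of whom 21% + 24% = 45% had BMI below 18.5 kg/m². Taking that as the exposure and carrying the share over gives n1 = 270 exposed and n0 = 330 unexposed;
- two-sided alpha 0.05 (an assumption; the article does not state alpha).

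With k = n1/n0 = 0.818 and d = 0.075:

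p̄ = (330 × 0.07 + 270 × 0.145)/600 = 62.25/600 = 0.10375

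n0 = [1.96·√((1 + 1/k)·p̄(1 − p̄)) + 0.842·√(p0(1 − p0) + p1(1 − p1)/k)]² / d² = (0.891 + 0.392)² / 0.005625 ≈ 293

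Continuity correction: n0 × ¼[1 + √(1 + 2(1 + 1/k)/(n0·d))]² ≈ 322, or about 586 in total, against 600 expected. At 330 v 270 the power is 81.1% corrected and 84.4% uncorrected, so the stated 80% reproduces.

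For CICADA, 635 of the 1947 participants with BMI recorded in Table 1 were below 18.5 (147 + 208 + 280). Applied to 1412, this gives about 461 v 951 and power of 98.7% corrected. There, 80% is a conservative floor.

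**3. What this says about the other versions.** The composite contains every 2-hour event, so its prevalence in each group is at least that of the 2-hour outcome. The diabetes-only version drops impaired glucose tolerance and adds HbA1c, so it could be higher or lower. No rate is given for either, and their power cannot be computed from the article.

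**4. Treated diabetes scored as unaffected: an illustration only.** Suppose a share m of true events, equal in both groups, has treated diabetes with 2-hour glucose below 7.8. Both rates are multiplied by (1 − m), and so is the contrast.

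| m (assumed) | Rates | Difference | St-ATT power, corrected | Uncorrected |
|---|---|---|---|---|
| 0 | 7.0% v 14.5% | 7.5 points | 81% | 84% |
| 10% | 6.3% v 13.05% | 6.75 | 76% | 80% |
| 20% | 5.6% v 11.6% | 6.0 | 70% | 75% |
| 30% | 4.9% v 10.15% | 5.25 | 63% | 69% |

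CICADA stays at or above 93% throughout. The article gives no value for m, so the table shows sensitivity and is not an estimate.

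**The case against.** The best defence is that Assessments simply puts the Outcome measures definition into operation. Both cover diabetes plus impaired glucose tolerance, the power statement follows Assessments, and HbA1c is described there only as a marker of longer-term control. On this reading a single question remains, the role of HbA1c. That narrows the conflict but does not remove it. The primary list says OGTT or HbA1c, and nothing in Assessments brings HbA1c back into the event.

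It is also fair that the Hypothesis 1 text never uses the word primary. It lists primary and secondary outcomes together, so its diabetes wording may be shorthand. A reader might infer three rival primary definitions; the article supports two, plus looser wording in two other places.

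Other stronger readings also fail:
- **Known diabetes is excluded.** No text says so. Participant recruitment makes only people who decline the OGTT ineligible ("People not consenting to either version of the OGTT, a) or b), will be considered as not consenting to SAMPA overall and thus ineligible"). That is a deliberate entry condition, and serum lipase, one of the exocrine outcomes, is itself taken from the baseline OGTT sample.
- **The St-ATT HbA1c figures in Table 1 (17% and a further 30%) size the problem.** They were measured in adults undergoing tuberculosis treatment, and the article itself attributes part of the milder band to tuberculosis. They are not prevalences at the SAMPA visit or counts of treated diabetes. Both primary definitions include pre-diabetes, so the gap between the bands does not measure how those two differ.
- **The HbA1c methods differ** (venous in DIVIDS, fingerprick in most other cohorts). Primary analyses are within cohort, so this touches pooled analyses only.

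Handling of treated diabetes could sit in a fuller plan. The conflict between the two primary definitions is in the article itself and cannot be deferred in that way.

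**Conclusion.** The inconsistency is real and rests on the text alone. Two sections label different events as primary, and two others describe diabetes without impaired glucose tolerance. Only the 2-hour glucose version has a stated event rate and a power statement. That statement is sound for St-ATT and conservative for CICADA, assuming two-sided alpha 0.05 and BMI below 18.5 kg/m² as the exposure.

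The treated-diabetes point follows from reading the 2-hour rule literally. Its direction is towards a smaller contrast if the affected share is similar in both groups. Its size is unknown, because the article does not say how many participants have diagnosed or treated diabetes. The documents do not support a claim that such people are excluded, or that the OGTT consent rule needs changing.

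**What to change.** State one primary endocrine outcome in identical words in Study objectives, Outcome measures, Assessments and the Hypothesis 1 analysis. The natural choice is the one already powered: 2-hour OGTT glucose at or above 7.8 mmol/L. Count previously diagnosed or treated diabetes as an event whatever the 2-hour value; if the investigators prefer the purely measured endpoint, run this as a prespecified sensitivity analysis. Name the HbA1c-based outcome and the diabetes-only outcome as secondary.

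The cost is small: wording in four places, and one diagnosis and treatment item that must feed the endpoint. HbA1c loses its primary status. Sample size, eligibility and visit procedures need not change.
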